### Sampling technique, randomization, concealment allocation and blinding

Permuted balanced block randomization will be conducted by the study supervisor to generate a random sequence of numbers to represent the two groups in an equal allocation ratio of 1:1. The random numbers will be labeled on concealed envelopes. The sealed envelopes will contain a folded opaque paper with letter A or B representing (chewing plus routine care) and (non-chewing plus routine care) groups respectively so that its not possible to deduce the assignment group based on random sequence numbers by the allocating team (research assistants). In addition, the envelope will have a similar stamp on the seal to be able to deduce possibility of breach of protocol (premature opening of the envelope). At this time both consent for surgery, information about the study and or consent to participate in the study will be obtained in writing at the emergency department. This is to avoid bias of recruiting participants after knowledge of intra-operative findings and to enable pre-operative care standardization between groups. The allocating team (trained research assistants) will give the envelope to the eligible participant 2 hours prior to surgery when a diagnosis of gut perforation is made from the radiological findings. The envelope will remain sealed until the patient enters the operating room and the participant will be unblinded just before induction of anesthesia where an instruction will be issued regarding chewing or not chewing any gum post-operatively. At this point an additional number either H, F or K will be added to the sequence number on the envelope to form participant identification number (PIN) to represent HRRH, FRRH, KIUI-TH for tracking records of recruitment and representation from each hospital. The outcome assessors (attending physicians) will be blinded throughout about the ongoing study since chewing gum is not known to cause adverse effects that would warrant un-blinding. The recruiting team will be totally different from the outcome assessors.

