### Data management

The data collection forms will have patient PIN code instead of names and will only be accessible to investigators. Hard copy records will be kept in a locked cabinet until 6 months following completion of the study and thereafter will be destroyed. Electronic records will be kept in a password protected file on the investigator’s password protected computer, and on completion of the study, they will be saved on a Digital Versatile Disc (DVD) that will be submitted to KIU registry and to a peer reviewed journal’s permanent data repository link for accessibility and reusability by other researchers.

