## Discussion

Previous researchers have not focused on acute peritonitis due to gastroduodenal perforations when assessing effect of chewing gum on ileus which this study is set to address. In their findings so far, there is compelling evidence to suggest that chewing gum plays a role in resolution of ileus [9,12], although controversial findings have been reported as well [28]. Our study is timely to shade more light in the context of low resource settings that are often under-represented in research publications.

Readily available and affordable chewing gum could offer benefit of reducing prolonged post-operative ileus and result in an added advantage of being discharged through a short-hospital-stay track. This protocol seeks to generate level one evidence regarding the role of chewing gum in resolution of ileus among patients with peritonitis due to gastro-duodenal perforations.

The generalizability of our study is limited by relatively smaller sample size and excluding patients with comorbidities but we hope our findings could be used to benchmark larger future multi center randomized controlled trials. More so, in this study, the participants will be un-blinded early since any placebo in this case would also count as sham feeding. We will only enroll patients with peritonitis due to gastroduodenal perforations which may not have a high bacterial burden compared to other gastrointestinal perforations thus generalizability of results will be limited in this context.

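### The participant identification number is completed only after the arm is revealed, with no earlier enrolment entry described, so a revealed allocation could be lost from the comparison

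*Protocol article*

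**What the plan says.** The section on sampling technique, randomization, concealment allocation and blinding (protocol article, Methods) sets out this order:

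- The list, with 1:1 allocation: "Permuted balanced block randomization will be conducted by the study supervisor to generate a random sequence of numbers to represent the two groups". Of the envelopes it says: "The random numbers will be labeled on concealed envelopes". The arm letter is on folded opaque paper inside, and a stamp across the seal is meant to show premature opening.
- Written consent is taken in the emergency department.
- Research assistants give the envelope to the eligible participant 2 hours before surgery.
- The reveal: "The envelope will remain sealed until the patient enters the operating room and the participant will be unblinded just before induction of anesthesia".
- The identity, called the PIN: "At this point an additional number either H, F or K will be added to the sequence number on the envelope to form participant identification".

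The Data management section adds: "The data collection forms will have patient PIN code instead of names". The section on participant recruitment and study procedure lists the PIN among the particulars entered on the data collection form.

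Three places provide for removal. Exclusion Criteria include being unconscious or unable to chew after 24 hours post-surgery. The text under Figure 1 terminates participants for any breach of the pre- or post-operative protocol. Termination from the study names cross-over, breach of allocation and loss to follow-up. Data processing and analysis states that the intention-to-treat model will be used.

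**The concern.** A randomised comparison is protected when a patient is irrevocably in the trial before anyone knows the arm. Here the last step of identification follows disclosure, and the data form is keyed to the identifier completed at that step. If someone in theatre or on the ward decides, knowing the arm, that a patient does not belong in the trial, the stated procedure has no earlier entry against which the loss would show.

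The removal rules make such decisions look legitimate. Ability to chew after 24 hours and adherence can only be judged once the arm is known, and ability to chew has a practical consequence mainly in the gum arm. If losses relate to recovery and fall more on one arm, the primary comparison of time to resolution of ileus is biased. With 52 patients, or 52/2 = 26 per arm, each patient is 1/26 = 3.8% of an arm.

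**Working it through.** The plan gives no figure on this point, so there is none to reproduce. The check is one of sequence, followed by an illustration of size.

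**Sequence**

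| Step | When | Before the arm is known? |
|---|---|---|
| Written consent | Emergency department | Yes |
| Numbered envelope handed over | 2 hours before surgery | Yes |
| Enrolment entry naming patient and number | Not described | – |
| Envelope opened | Operating room, just before induction | This is the reveal |
| Hospital letter added, PIN complete | At that point | No |
| Data form carrying the PIN | Cannot be complete until the PIN exists | No |
| Exclusion for inability to chew | After 24 hours post-surgery | No |
| Termination for non-adherence or loss to follow-up | During follow-up | No |

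**What the safeguards cover.** The opaque paper hides the content of one envelope. The stamp shows premature opening. Neither bears on what happens after a proper opening.

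**Size, under stated assumptions.** Inputs: 52 patients (article), hence 26 per arm. Assumed: no true gum effect, normally distributed outcome with SD 1, pooled t-test at two-sided 0.05. Also assumed: k gum patients are dropped after the reveal and replaced, and they are exactly the k slowest to recover.

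For k = 1, take 27 gum patients and remove the largest value. The expected maximum of 27 standard normal values is about 2.0, so the mean of the remaining 26 shifts by about 2.0/26 = 0.077 SD in favour of gum. Simulation gives:

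| Dropped (k) | False benefit (SD) | Type I error |
|---|---|---|
| 0 | 0 | 5% |
| 1 | 0.07 to 0.08 | about 7% |
| 2 | 0.13 to 0.14 | about 9% |
| 3 | 0.19 | about 13% |

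This is the worst case for a given k, because selection tracks the outcome perfectly. A patient dropped in theatre could be chosen on prognosis only, which gives less. If the dropped patients are a random subset of the gum arm, the error stays at about 5%. The illustration needs no assumption about block size.

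**The case against.** The best defence is that the patient is already tied to the trial before the reveal. Consent is signed, a pre-numbered envelope is in the participant's hands 2 hours earlier, and only the hospital letter is added in theatre. A dropped patient would leave a signed consent and a gap in the numbers. Screening logs and envelope accounting are operational details that an article may leave to the full protocol, and intention to treat is stated.

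Much of this stands. It would be wrong to say that the participant has no trial identity before the reveal, and a gap would be visible if envelopes are reconciled. But the objection relies on steps the article does not describe, and a gap in the numbers does not by itself say which patient is missing. The point is not an omitted detail: the article states the order of events, and puts completion of the identifier on the wrong side of the reveal.

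A reader might infer something stronger: that staff can predict later assignments, because blocks are balanced, envelope numbers are visible and "the participants will be un-blinded early since any placebo in this case would also count as sham feeding". The article does not support this. It does not give the block size, say whether the size varies, or say whether there is one list or one per hospital, and an article may leave these out. Prediction needs small fixed blocks of known size, numbers that follow list order, and recruiters who learn earlier arms. Under those assumptions, with a separate list per site, the share of correct guesses for a block of 4 is [2 + 2³/6 − 1/2]/4 = 0.708, and 33% of assignments are certain. With one list shared by three sites, and staff knowing only their own site's arms, these fall to about 57% and 4%. Type I errors of 9% to 14%, obtained by assuming that recruiters shift prognosis by 0.25 SD according to their guess, belong to the first case only and are an assumed worst case. Putting the sequence number in the PIN adds little, since recruiters already know enrolment order.

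**Conclusion.** The concern holds as a weakness in the stated order of registration. The PIN is completed after the arm is known, no earlier enrolment entry is described, and the stamp does not guard against loss after a proper opening. Removal after the reveal is allowed in three places and sits uneasily with the intention-to-treat statement, though the article does not say that removed patients are left out of the analysis. The consequence is a risk, not a demonstrated bias. Its size depends on how many patients are lost and how closely the losses follow recovery: from no inflation if they are random to about 13% type I error if the three slowest gum patients are lost and replaced. Predictability of later assignments remains a conditional risk that the text does not establish. Because the trial is small and the remedy nearly free, the change should be made.

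**What to change.** In the section on sampling technique, randomization, concealment allocation and blinding, move the identification step to hand-over:

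1. Form the full PIN (sequence number plus hospital letter) when the envelope is given to the participant.
2. Write it, with date and time, on the still-sealed envelope and in the trial log.
3. Issue envelopes strictly in numerical order.
4. State that every patient so registered counts as randomised in the intention-to-treat analysis, and reconcile the removal passages with that sentence.

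The cost is a small amount of record keeping at hand-over, with no extra staff, visits or patients. The price in analysis is that patients removed after the reveal stay in the denominator. No change to the form of the PIN is needed to hide its list position.

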**Methods::**

This will be a randomised controlled trial done in 3 hospitals. Fifty-two patients will be randomised to 2 groups. Group A will receive chewing gum in addition to routine care, whereas group B will receive routine care only. The duration of post-operative ileus in the two groups which is the primary outcome, will be compared using the independent samples t-test in SPSS version 22. The length of hospital stay, in-hospital morbidity and mortality will be the secondary outcomes. This trial has been approved by Kampala International University research and Ethics committee (Ref No. **KIU-2021-60**) and Uganda national council of science and technology (Ref No. **HS1665ES**). Retrospective registration with the research registry has also been done (UIN: researchregistry8565).

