### Eligibility criteria

#### Inclusion Criteria

All patients with confirmed gastric or duodenal perforation, between the age of 18 and 65 will be included. The upper age limit will be used because increasing age increases the risk of PPOI [10] yet we want the groups to be comparable.

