### Sample size estimation

Using the formula; 
N = 2\; \times \,{({\textstyle{{{Z_{1 - \alpha /2}}\; + {Z_{1 - \beta }}} \over \delta }})^2} \times {S^2}
 for determining sample size in randomized clinical studies with a statistical superiority design [27], and findings from a study that evaluated effect of chewing gum following pancreatic-duodenal surgery in Sweden [28], 46 participants per group will be required. On adjusting the sample size to the finite population and adding 10% to improve internal validity, the required sample size will be 52.

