### Participant recruitment and study procedure

Patients admitted in emergency department (ED) with suspected gastric or duodenal perforation based on clinical and radiological assessment will be evaluated for eligibility and considered as possible candidates for the study.

Routine pre-operative management for GDP will be done for all patients including; taking vital signs like; Blood pressure (BP), pulse rate (PR) respiratory rate (RR), oxygen saturation (SPO2) and temperature plus continuous monitoring, passing Foley’s urethral catheter and monitoring urine output, passing two large bore cannulas, fluid resuscitation with IV Normal saline till urine output is >0.5 mls/h, nasogastric tube insertion, nil by mouth, intravenous (IV) ceftriaxone 2 grams (g), IV metronidazole 500 milligrams (mg), IV Paracetamol 1g, IV omeprazole 40 mg, doing complete blood count (CBC), doing blood grouping and cross match, serum electrolytes, and obtaining informed consent for emergency laparotomy.

After resuscitation, the patients will be taken for laparotomy under intubation general anesthesia. Patient’s particulars will be recorded in the data collection form including participant identification number (PIN), age, address, presenting symptoms and duration of symptoms among others as shown in appendix I. The type of perforation surgery will be recorded.

Post operatively patients in both groups will receive all the routine post-operative care. This will include IV Normal saline and 5% dextrose in the ratio of 2:1, which will be prescribed for the first 24 hours with the total volume determined by the 4:2:1 rule for calculating maintenance fluids. The fluid prescriptions that follow, will be according to fluid balance chart. Other post-operative instructions will include; IV ceftriaxone 2g once a day (OD) for 5 days, IV metronidazole 500mg 8 hourly for 5 days, IV Omeprazole 40mg OD till oral feeding is initiated, IV Paracetamol 1g 8 hourly till oral feeding is initiated, Oral warm water will be started on first POD, early removal of NGT will be done, ambulation will be encouraged from first POD [14,25]. In addition to the above, patients in group A will receive chewing gum and below is a clear instruction on how they will use it. Figure 1 shows a flow chart summarizing the study procedure.

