### Data processing and analysis

The intention to treat model will be used during analysis to minimize bias. Summarized data will be analyzed using Statistical Package for the Social Sciences (SPSS Inc., Chicago, USA, version 22.0 for Windows). Continuous variables will be presented as the mean ± standard deviation. Categorical variables will be expressed as frequencies.

To compare the time taken for post-operative ileus to resolve and length of hospital stay, normality of distribution will be assessed using the Shapiro-Wilks test. If the data are found to be normally distributed, then equal variance for the two groups will be determined using Levene’s test hence two sample t-test will be computed assuming equal or unequal variance as appropriate. If the data are not normally distributed in both groups, the nonparametric Wilcoxon Rank sum (Mann-whitney U) test will be used to compare the difference in means. To compare the in-hospital morbidity and mortality, the chi squared test will be used. All analyses will be performed at 95% confidence level and a p value ≤0.05 will be considered significant.

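### Allocation as described is one blocked sequence with hospital recorded only for tracking, and the primary test is unadjusted: a modest, cheaply recovered loss of balance and precision, not a bias.

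*Protocol article*

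**What the plan says.** **Allocation.** Under the heading on sampling, randomization, concealment and blinding, the article states: "Permuted balanced block randomization will be conducted by the study supervisor to generate a random sequence of numbers to represent the two groups". The ratio is 1:1. No stratification factor and no block size are named. The hospital is attached when the envelope is opened in the operating room: "At this point an additional number either H, F or K will be added to the sequence number on the envelope". The stated purpose of the letter is to track recruitment and representation by hospital.

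**Sites.** The study setting section lists three hospitals of about 600, 333 and 700 beds, with 3, 2 and 6 general surgeons and 2, 3 and 30 senior house officers. The senior house officers operate under supervision.

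**Age.** The inclusion criteria give the reason for the 18 to 65 limit: "The upper age limit will be used because increasing age increases the risk of PPOI [10] yet we want the groups to be comparable".

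**Recorded baseline data.** The data form includes "age, address, presenting symptoms and duration of symptoms among others". The participant number carries the hospital.

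**Primary test.** The data processing section fixes a two-sample t-test if the data are normal and a Wilcoxon rank-sum test if they are not. Neither has a hospital term or a covariate.

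**Size.** "Fifty-two patients will be randomised to 2 groups", or about 26 per arm.

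**The concern.** A blocked sequence balances the arms along the sequence. If consecutive numbers are used in different hospitals, each block is divided between sites and the arms are no longer balanced within any one of them. The sites differ in size and staffing, so a trialist would usually make hospital a stratum.

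The protocol also names a prognostic variable and states the aim of comparable groups, but relies on an age limit to achieve it. A limit narrows the age range. It does not balance age between the arms or remove the outcome variation due to age within 18 to 65.

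At stake are the credibility of a 52-patient comparison with a visible imbalance in one hospital, and some precision that could be had from data already on the form.

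**Working it through.** **1. The plan's own figure.** The sample size section gives "46 participants per group will be required" and then: "On adjusting the sample size to the finite population and adding 10% to improve internal validity, the required sample size will be 52". The 46 cannot be reproduced, because the article states no difference, SD or power. Its formula can be turned round to give the standardised effect: d = √(2/46) × (z₀.₉₇₅ + z₁₋β).
- At an assumed 80% power: d = 0.2085 × (1.960 + 0.842) = 0.584.
- At an assumed 90% power: d = 0.2085 × (1.960 + 1.282) = 0.676.

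The two-sided 5% level follows from the formula and from "a p value ≤0.05 will be considered significant".

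**2. Balance within hospitals.** Inputs: 52 patients and 1:1 blocks on one sequence (from the article). Block size 4 and recruitment shares of 42/36/22% are assumptions; the shares roughly follow bed numbers (700/1633 = 43%, 600/1633 = 37%, 333/1633 = 20%). Each patient was assigned to a hospital at random with these shares, and the arm split was counted in each hospital over 20,000 simulated trials.

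| Assumed shares | At least one hospital split 65:35 or worse |
|---|---|
| 42/36/22% | about 36% |
| equal | about 31% |

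Blocks of 6 change these figures by about one point. The smallest hospital, with about 11 patients, contributes most: it crosses the cut-off in about 26% of trials.

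**3. Power with and without adjustment.** Take 26 per arm and k covariate terms that explain a share R² of the outcome variance. Degrees of freedom are 50 − k. The noncentrality is

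d × √(26/2) × √[(df − 1)/(df + k − 1)] / √(1 − R²),

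where the middle root allows for chance covariate imbalance. Power comes from the noncentral t distribution.
- Unadjusted, d = 0.584: 0.584 × 3.606 = 2.106 on 50 df; power 54.2%.
- Four terms (two for hospital, age, symptom duration), R² = 0: 2.106 × √(45/49) = 2.018 on 46 df, critical value 2.013; power 50.6%.
- Four terms, R² = 0.2: 2.018/√0.8 = 2.257; power 59.8%.

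The documents give no R², so a range is shown:

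| Model | R² = 0 | 0.1 | 0.2 | 0.3 |
|---|---|---|---|---|
| Four terms, d = 0.584 (unadjusted 54.2%) | 50.6% | 54.9% | 59.8% | 65.6% |
| Four terms, d = 0.676 (unadjusted 66.6%) | 62.8% | 67.4% | 72.5% | 78.0% |
| Hospital and age only (k = 3), d = 0.584 | 51.6% | 55.8% | 60.8% | 66.6% |
| Age only (k = 1), d = 0.584 | 53.3% | 57.7% | 62.7% | 68.5% |

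With four terms the break-even is near R² = 0.1. Age alone costs under 1 point if it explains nothing and gains about 3.5 points at R² = 0.1.

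**4. How far chance imbalance can move the result.** The part of the arm difference due to imbalance in the covariates has SD √(R² × 2/26), which is 0.088, 0.124 and 0.152 SD at R² = 0.1, 0.2 and 0.3. The effect of 0.584 SD is 6.7, 4.7 and 3.8 times as large. Half the effect is reached in about 0.1%, 2% and 5% of trials.

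**The case against.** The strongest reply is that nothing here is invalid. An unadjusted comparison after unstratified randomisation is a correct test, and its standard error already contains chance imbalance. This stands.

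A reader might infer from 26 per arm that chance imbalance could be as large as the effect sought. Step 4 shows that it practically never is: the probability is about 1 in 10,000 even at R² = 0.3.

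A reader might also shrink the SD by √(1 − R²) and stop there, which gives power of 59/64/69% at R² = 0.1/0.2/0.3, or the worth of 58/65/74 patients. That ignores the price of four terms in 52 patients. At R² = 0.1 the net gain is under one point.

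The staffing figures invite the inference that feeding, tube removal and discharge are decided locally. The article does not say so. It sets common routine care for both groups and has adherence checked in the treatment charts. Staff numbers alone do not show that ileus lasts longer at one site. Symptom duration is recorded but never called prognostic.

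Finally, a single list shared patient by patient is a reading of the text. Whole blocks sent to each hospital would give near balance within site, and a condensed article may omit envelope logistics. This also stands, but the article gives the letter a tracking purpose only and names no stratum. The unadjusted primary test is a stated choice, not a detail left open.

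**Conclusion.** The point holds as a modest efficiency recommendation. As described, randomisation does not protect balance within hospitals, and the primary test makes no use of a variable that the protocol itself calls prognostic.

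The chance of a noticeably uneven split in at least one hospital is roughly one in three, given the assumed block size, shares and 65:35 cut-off. The precision gain depends on an R² that the documents do not give: about 6 points of power at 0.2 and 11 at 0.3 with four terms, nothing at 0.1, and a loss of about 3.5 points at 0. The case is firmest for age, on the protocol's own words. It is plausible for hospital and open for symptom duration.

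Adjustment does not repair the separate reduction from 46 per group to 52 in total, which by itself leaves about 54% power at the 80%-based effect and 67% at the 90%-based one.

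**What to change.** 1. Generate a separate permuted-block list and envelope set for each hospital, with varying, undisclosed block sizes. If whole blocks are already sent to each site, say so. Registration was retrospective, so recruitment may have made this step too late.
2. Before the data are examined, prespecify as primary a linear model for time to resolution (on log hours if skewed) with treatment, hospital and age. Add symptom duration only if it is judged prognostic on grounds given in advance.
3. Keep the unadjusted t-test or rank-sum test as a supportive analysis.

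**Cost.** Three lists instead of one, one model statement, and no new data. Hospital and age use three degrees of freedom; if they explain nothing, power falls from about 54% to 52%. All four terms would take it to about 51%, which is the reason to keep the model short.

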### Chewing gum administration

Green PK brand of chewing gum will be used in this study since a pilot survey done before data collection showed that majority of the people preferred the green flavor (*appendix II, unpublished data*). We will use one flavor to minimize bias. The patients in Group A will be given green flavored PK and will start chewing after regaining consciousness. The patients will chew 2 pellets of PK till they are tasteless three times in a day (morning, afternoon, and evening). After chewing, the patients will be encouraged to rinse the mouth with clean water. The patients will stop chewing gum when POI resolves. Resolution of POI will be defined as passage of stool or flatus or both in addition to full filling the criteria defined in the 6 domains described by the Tripartite gastrointestinal recovery post-operative ileus group such as absence of nausea and vomiting, having no need of nasogastric intubation, absence of abdominal pain and distension, and ability to tolerate oral feeds [29]. Each patient will be offered a watch, notebook, and pen and with the help of the caretaker, record every day’s events and the time they occur. The events recorded will include; time when gum is chewed, flatus passed, stool passed, vomited or hunger felt. The outcome assessors will do clinical evaluation 6 hourly and information will be recorded in the data collection form (appendix I).

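### Assessor blinding is claimed without a masking method, and the protocol's own procedures make it doubtful for a primary outcome that rests partly on judgement

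*Protocol article*

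**What the plan says.** All references are to the protocol article.

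- **The claim** (Sampling technique, randomization, concealment allocation and blinding): "The outcome assessors (attending physicians) will be blinded throughout about the ongoing study". The reason follows at once: "since chewing gum is not known to cause adverse effects that would warrant un-blinding".
- **Separation of teams** (same section): "The recruiting team will be totally different from the outcome assessors".
- **Opening of the allocation** (same section): "The envelope will remain sealed until the patient enters the operating room and the participant will be unblinded just before induction of anesthesia". The patient is told there whether to chew gum after surgery.
- **Assessment** (Chewing gum administration): "The outcome assessors will do clinical evaluation 6 hourly and information will be recorded in the data collection form (appendix I").
- **Patient-kept record** (same section): each patient, helped by the caretaker, keeps a notebook. "The events recorded will include; time when gum is chewed, flatus passed, stool passed, vomited or hunger felt".
- **Visibility of the intervention** (same section): group A chews in the morning, afternoon and evening until ileus resolves.
- **Endpoint** (same section and Study variables): the time from end of surgery until flatus or stool has been passed and further criteria are met. These cover nausea and vomiting, need for a nasogastric tube, pain and distension, and tolerance of feeds.
- **Access to the form** (Data management): the data collection forms "will only be accessible to investigators".
- **Disclosure** (Discussion): participants are unblinded early because any placebo would itself act as sham feeding. Nothing is said about assessors.

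**The concern.** The article states a strong property, that assessors are unaware even of the study, but the reason offered does not deliver it. The absence of adverse effects explains why an emergency code break is unlikely. It does not explain how a physician on the ward is kept from learning who chews gum. A separate recruiting team protects enrolment and leaves outcome assessment untouched.

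The primary outcome is exposed to this. Flatus and stool are reported by a patient who knows the arm. The remaining components, such as distension, need for a tube and tolerance of feeds, call for judgement. A physician who knows the arm and expects gum to work may accept resolution one visit earlier in group A. A reader who trusts the blinding statement would give the result more credit than the design earns.

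**Working it through.** **Step 1: passages side by side.** The protocol states no figure on this point, so the check is mainly textual.

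| Needed for the claim to hold | What the text provides |
|---|---|
| Assessors unaware of the study | They evaluate patients every 6 hours and the findings go on the study's form. Data management limits that form to investigators. Either the assessors know of the study, or someone not named records their findings. |
| Assessors unaware of the arm: gum not seen | Three chewing sessions a day; no step hides the gum at assessments. |
| Assessors unaware of the arm: records do not reveal it | Gum times are listed with flatus, stool, vomiting and hunger. Anyone who uses this record to time flatus sees the arm. |
| Assessors unaware of the arm: allocation not overheard | The instruction is given in the operating room; no step keeps assessors away. |
| A stated masking method | None. The reason given concerns adverse effects. |

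**Step 2: where judgement enters.** Resolution requires flatus or stool and the other criteria. The judged components cannot bring resolution forward to before the bowel event. Where that event comes first, they set the time.

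**Step 3: what one visit could do (illustration only).**

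Inputs:
- 52 patients at 1:1, so 26 per arm (Sample size estimation; the randomization section).
- Significance level 0.05 (Data processing and analysis), taken as two-sided from the sample size formula.
- Shift of 6 h, one assessment interval, applied to every group A patient, with no true effect.
- SD of time to resolution: not in the document; assumed 12, 24, 36 or 48 h.

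Formulas, with a normal approximation: λ = (6/SD)/√(2/26), where √(2/26) = 0.277. Rejection probability = 1 − Φ(1.96 − λ) + Φ(−1.96 − λ).

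| Assumed SD (h) | 6/SD | λ | Type I error |
|---|---|---|---|
| 12 | 0.50 | 1.80 | 0.438 |
| 24 | 0.25 | 0.90 | 0.147 |
| 36 | 0.17 | 0.60 | 0.092 |
| 48 | 0.125 | 0.45 | 0.074 |

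With an average shift of 3 h and the same SDs, the values are 0.147, 0.074, 0.060 and 0.056.

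**The case against.** The strongest reply is that a clinician can examine a post-laparotomy patient every 6 hours without knowing the hypothesis or the arm. Gum is not chewed continuously, the notebook belongs to the patient and caretaker, and research assistants could transcribe ward findings. Flatus and stool are discrete events that limit how early resolution can be called. Appendix I and Figure 1 are not available, and an article may leave bedside handling of records to the full protocol.

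Much of this stands, and it rules out several stronger readings that a reader might infer:

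- *The assessors are effectively open-label.* This is explicit for participants only. For assessors the text shows an unsecured claim, not a known failure.
- *The physicians fill in the study form.* The sentence is passive and names no recorder.
- *The assessors are in theatre when the envelope is opened, or they read the notebook.* Neither is stated; nothing prevents either.
- *The same physicians decide on feeding and tube removal, or tell group A to stop chewing.* No decision-maker is named for these.
- *A one-visit shift is a given share of the planned effect.* Sample size estimation gives no power, difference or SD, so there is no planned effect to compare with.

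The illustration is also a hard case, since it moves every group A patient by a full visit. The average 3 h shift gives much less inflation except at the smallest SD.

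The contradiction on the page remains. An article may omit masking detail, but this one makes a positive claim, gives a reason that does not support it, and describes procedures that work against it.

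**Conclusion.** The concern holds in this limited form: the article claims that assessors are blind throughout, names no method that would achieve it, and sets out procedures that make it doubtful. Because resolution depends partly on judgement, assessor knowledge of the arm could bias the primary outcome, and the stated limitations do not warn of this.

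The size of any bias cannot be derived from the document. If every group A patient were called one visit early, the 5% error rate would become about 44% at an SD of 12 h and about 7% at 48 h. That range rests on assumed SDs, 26 per arm, a uniform 6 h shift and a normal approximation. The textual finding does not depend on it.

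This should be corrected. It is not evidence that assessment will in fact be biased.

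**What to change.** 1. Record bowel and symptom events on a sheet that is identical in both arms. Record gum times on a separate sheet that assessors do not see.
2. Keep gum and the gum sheet out of sight at the 6-hourly assessments.
3. Give the allocation instruction out of the assessors' presence.
4. Reconcile the blinding section with Chewing gum administration and Data management: say who records the assessors' findings and what the assessors know of the study.
5. Reword the blinding statement to say that assessors are masked to allocation as far as possible and that participants are not.
6. Add imperfect assessor masking and patient-reported flatus and stool to the limitations in the Discussion. Separate sheets do not remove reporting bias from unblinded patients.

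The cost is one extra sheet, handled by the existing research assistants. Patients and caretakers already write down gum times, so the recording itself is not new. Masking will still be imperfect, and the blinding statement will read less favourably than it does now.
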